##### TCM symptom assessment

4.1.2.3

TCM symptom grading scale for pancreatic cancer is based on the common symptoms of pancreatic cancer. It is used to observe pre- and post-treatment symptom improvement and includes 13 symptoms: poor appetite, low food intake, fatigue, jaundice, nausea and vomiting, abdominal distension, pain, fever, spontaneous sweating, loose stools, constipation, and insomnia. Each symptom has 4 grades, namely: none, mild, moderate, and severe, with corresponding scores of 0, 1, 2, and 3. The higher the score, the more severe the symptom.

#### Quality of life assessment

4.1.3

The EORTC Core Quality of Life Questionnaire (EORTC QLQ-C30) is a core scale for quality of life analysis of cancer patients developed by The European Organization for Research and Treatment of Cancer (EORTC). Because of its reliability and validity, it is widely used in the assessment of quality of life of all cancer patients. The Quality of Life Questionnaire pancreatic cancer module (QLQ-PAN26) is a module designed according to specific characteristics of pancreatic cancer and is used to evaluate the symptoms, side effects, and quality of life of pancreatic cancer patients. It has been widely used in clinical trials and studies of pancreatic cancer in recent years.^[15,16]^

EORTC QLQ-C30 consists of 5 functional subscales (body, role, cognitive, emotional, and social functions), 3 symptom subscales (fatigue, pain, and nausea and vomiting), and a general health status subscale, as well as several single items. The higher the scores of functional subscales and general health status scale, the better the quality of life. The higher the score of symptom subscale, the worse the quality of life. QLQ-PAN26 includes cancer pain, digestive symptoms, and satisfaction with health care. The higher the severity of these indicators, such as fatigue and pain, the higher the score, suggesting poorer quality of life for pancreatic cancer patients.^[17]^

#### Body condition assessment

4.1.4

Eastern Cooperative Oncology Group (ECOG) in the United States has developed a simplified activity status rating scale, which is an indicator for evaluating the general health status and treatment tolerance of patients with grades 0 to 5. It is generally considered that patients with activity level 3 or 4 are not suitable for chemotherapy.^[18]^

#### Imaging assessment

4.1.5

Imaging evaluation includes the application of CT, type-b ultrasonic, MRI, etc to objectively evaluate the therapeutic effect.

Each participant has a CRF, and all relevant data will be recorded in it. Two clinical research associates supervise the whole research process.

### Safety assessment

4.2

Routine blood tests and liver and kidney function tests are assessed at baseline, and functional damage is assessed at each follow-up visit. In addition, the investigator will ask subjects at each visit whether there are any adverse events (AEs), including physical discomfort or impairment. If there are any AEs, the investigator would provide appropriate treatment to the patient immediately and record it in the CRF at that time. Adverse effects are evaluated according to the National Cancer Institute (NCI) Common Terminology Criteria for Adverse Events.

### Data management

4.3

#### Data recording

4.3.1

The data are required to be filled in uniform CRFs completely and accurately in a timely manner without missing items.

#### Data monitoring

4.3.2

During the study, the supervisor will: check the informed consent and screening and inclusion status of the subjects in the cooperating units regularly, confirm that the filled content of the CRF is consistent with the original data, verify the withdrawal and loss of the enrolled subjects, record the reasons in the CRF, and confirm that all adverse events are documented.

#### Data management

4.3.3

Data managers are responsible for data entry and data re-verification. If problems are found, they should be registered and reported in time so as to deal with them quickly. All errors and modification of results should be recorded and properly preserved to ensure the quality of the data.

#### Data analysis

4.3.4

All statistical analyses will be performed using Statistical Packages of Social Sciences software (SPSS). A one-sided test (validity) will be used for all major efficacy indicators, and *P* values ≤.05 will be considered statistically significant. The measurement data will be expressed as the mean ± standard deviation, and the count data will be expressed using frequency and percentage. For quantitative indicators such as age, it is necessary to check whether the data meet the precondition of normality and homogeneity of variance. If the above conditions are met, a *t* test of measurement data of group design will be adopted. If only normality and not homogeneity of variance are satisfied, the calibration *t* test of measurement data in group design will be adopted. Otherwise, the Wilcoxon rank sum test will be used. For qualitative indicators such as sex, the general chi-square test will be performed according to the statistical analysis method corresponding to the data of the contingency table. If there is a frequency with a theoretical frequency <5, Fisher exact test will be used to directly calculate the exact probability. For survival data, the survival limit will be used to calculate the survival times of 25%, 50%, and 75% of each cohort. The log-rank test will be used to compare the survival rate, and the corresponding survival curve will be obtained.

For the analysis of influencing factors of efficacy, the univariate Cox regression model will be adopted in the first screen (*P* < .10), and the screened variables will then be fitted to the multivariate Cox regression model (*P* < .05).

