### Sample size calculation

3.5

The sample size calculation formula is as follows: 

[figure not shown]

In the above formula, *N* is the number of samples in each group, *p*_0_ is the incidence of outcomes in the non-exposed group, *p*_1_ is the incidence of outcomes in the exposed group, *c* is the ratio of the number of non-exposed and exposed groups, *α* is an acceptable type I error, *β* is an acceptable type II error, and *Z*_α_ and Z_*β*_ can be determined by looking them up in the *Z* value table.

The 1-year survival rate is expected to be 22% in the non-exposed group and 45% in the exposed group. Assuming a non-exposed group and an exposed group sample ratio of 1:1, the required sample size is estimated by SAS 9.4 software ([name]) to be at least 134 cases in the 2 groups, based on a 2-sided alpha at a significance level of 0.05 and the test efficacy 1-beta of 80%. Meanwhile, considering a dropout rate of 15%, we concluded that a total of 148 patients would need to be recruited to ensure significant results.

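### The sample size is planned at two-sided 0.05, but efficacy is tested one-sided at P ≤ .05, which doubles the nominal chance of a false claim for TCM

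*Protocol article*

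**What the plan says.** Sample size calculation (3.5) fixes the design standard. The calculation is "based on a 2-sided alpha at a significance level of 0.05", with 80% power. It assumes that "The 1-year survival rate is expected to be 22% in the non-exposed group and 45% in the exposed group" and that the groups are of equal size, and it arrives at a requirement "to be at least 134 cases in the 2 groups" before dropout.

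Data analysis (4.3.4) fixes the decision rule: "A one-sided test (validity) will be used for all major efficacy indicators". The same sentence goes on to say that P "values ≤.05 will be considered statistically significant".

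The Abstract names overall survival as the main efficacy index, and section 4.1.1 makes it the primary outcome. The one-sided rule therefore applies to the primary comparison. Nowhere does the article halve the threshold for the one-sided test, state its direction or explain the change from section 3.5.

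**The concern.** One study cannot run on both rules. Two-sided 0.05 allows a 2.5% nominal chance of a false claim in each direction. One-sided 0.05 puts the whole 5% in the tested direction, so the critical value is the one that a two-sided 0.10 test would use. The total nominal error is 0.05 in both cases; what doubles is the chance of a false claim for the favoured treatment.

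Three things are at stake.

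- **The primary conclusion.** A result with one-sided P between 0.025 and 0.05 is positive under 4.3.4 and negative under the standard used in 3.5. Either section could be cited once the data are known.
- **The stated operating characteristics.** The 80% power and the 134 patients describe a test that 4.3.4 does not use.
- **The possibility of harm.** Treatment is not randomised, so shorter survival in the integrated group is a real possibility. A one-sided test for superiority cannot declare it significant.

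**Working it through.** **Inputs (section 3.5 unless noted).** p0 = 0.22, p1 = 0.45, difference d = 0.23, mean p̄ = 0.335, ratio 1:1, power 80% (z = 0.842), alpha 0.05 two-sided (z = 1.960). Under the rule in 4.3.4, alpha is 0.05 one-sided (z = 1.645).

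**Step 1: reproduce the plan's 134.** The simple pooled formula for two proportions is

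n per group = 2 p̄(1 − p̄)(z_α + z_β)² / d²

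with 2 × 0.335 × 0.665 = 0.44555 and d² = 0.0529.

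- Two-sided: (1.960 + 0.842)² ≈ 7.849, so n = 0.44555 × 7.849 / 0.0529 = 66.1, rounded up to 67. The total is **134**, exactly as stated.
- One-sided: (1.645 + 0.842)² ≈ 6.183, so n = 0.44555 × 6.183 / 0.0529 = 52.1, rounded up to 53. The total is 106.

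The formula in the article is not legible here, so the common alternatives were also tried (totals for both groups):

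| Formula | Two-sided 0.05 | One-sided 0.05 |
|---|---|---|
| Simple pooled | 134 | 106 |
| Pooled under null, unpooled under alternative | 130 | 104 |
| Unpooled | 126 | 98 |
| Arcsine | 130 | 102 |
| Continuity-corrected | 148 | 120 |

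No one-sided version reaches 134. The two-sided alpha in 3.5 is therefore what produced the number, not a slip of wording.

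**Step 2: error in the tested direction.**

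- Two-sided 0.05: P(Z > 1.960) = 0.025.
- One-sided 0.05: P(Z > 1.645) = 0.05.
- Ratio: 0.05 / 0.025 = 2.

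**Step 3: power at 67 per group.**

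Power = Φ{[d√n − z_α √(2p̄(1 − p̄))] / √(p0(1 − p0) + p1(1 − p1))}

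with d√67 = 1.883, √0.44555 = 0.6675 and √(0.1716 + 0.2475) = 0.6474.

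- Two-sided: (1.883 − 1.960 × 0.6675) / 0.6474 = 0.887, so power is 81.3%.
- One-sided: (1.883 − 1.645 × 0.6675) / 0.6474 = 1.212, so power is 88.7%.

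**Step 4: the zone where the rules disagree.** At 67 per group and a pooled rate of 0.335, the smallest significant difference in one-year survival is z × 0.6675 / √67.

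- Two-sided: 1.960 × 0.6675 / 8.185 = 0.160.
- One-sided: 1.645 × 0.6675 / 8.185 = 0.134.

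An observed advantage between about 13.4 and 16.0 percentage points would be positive under one section and negative under the other.

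**The case against.** The contradiction itself is hard to dispute, so the case on the other side concerns its reach.

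- **The direction is not stated.** Section 4.3.4 never says which way the test points. This stands. Superiority of the integrated group is an inference from the word validity in the sentence and from the expected 45% versus 22%. It is the natural reading, and the silence is a further reason to rewrite the sentence.
- **The rule may not operate in practice.** Log-rank and chi-square tests are ordinarily reported with non-directional P values. If those were compared with .05, the error would already be 0.025 per direction. That is true, but the analyst would then be ignoring the written rule; the doubling follows when it is applied as written.
- **Harm would still be visible.** Section 4.3.4 also plans survival quartiles, survival curves and a Cox model whose sidedness is not stated, so shorter survival with TCM would show. This stands as far as it goes: the one-sided rule prevents a declaration of significant harm, not its display.
- **The power figures are not those of the log-rank test.** They compare one-year proportions and assume equal groups, while section 3.7 classifies patients only after data collection. This also stands. Steps 3 and 4 illustrate the mismatch; the doubling in step 2 does not depend on them.
- **Power is not harmed.** Correct: the sample was sized for the stricter rule. The defect lies in the evidential threshold alone.
- **The full protocol may justify the change.** A condensed article may omit a rationale. But both rules are explicit here and differ, and a rationale for one-sided testing would still leave the threshold at odds with the alpha used in 3.5.

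**Conclusion.** The concern holds. Sections 3.5 and 4.3.4 give incompatible decision rules for the primary outcome, and the planned sample size belongs to the rule in 3.5. Followed as written, 4.3.4 raises the nominal false-positive rate in favour of TCM from 0.025 to 0.05. At 134 patients, it moves the illustrative power from 81.3% to 88.7%.

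This is a wrong rule, not a missing detail, and it must be settled before outcome data are examined. The result assumes that the one-sided test is for superiority of the integrated group and that the P ≤ .05 threshold is applied to the one-sided P value. The error rates are nominal and take no account of confounding or of bias from the non-randomised grouping.

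**What to change.** In section 4.3.4, replace the one-sided rule with a statement that all efficacy tests, including the log-rank test for overall survival, are two-sided at the 0.05 level, and that effect estimates carry two-sided 95% confidence intervals. State that the P < .05 criterion for the multivariable Cox model is also two-sided. If a one-sided test is preferred, give its direction and set the threshold at 0.025, which is the same standard for a claim of benefit.

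The change costs one or two sentences and no patients, since 134 already rests on two-sided 0.05. The price is a stricter threshold for claiming benefit: results with one-sided P between 0.025 and 0.05 would no longer count as significant. If any outcome data have been examined before the change, the amendment should say so.

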### Determination of grouping

3.7

Patients will be divided into a non-exposed group (Western medicine treatment group) and an exposed group (integrated traditional Chinese and Western medicine treatment group), according to whether they will receive TCM treatment or not. The classification of the cohort is based on the time of exposure after all clinical data are collected, not set at the time of enrollment.

1.Western medicine treatment group: times of chemotherapy ≥2 courses.2.Integrated traditional Chinese and Western medicine treatment group: TCM treatment ≥12 weeks, times of chemotherapy ≥2 courses, TCM and Western medicine treatment can be performed simultaneously or before and after.

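### The test for quantitative indicators is picked from checks on the same data, so the 5% level is not guaranteed: about 6-7% if the smaller group happens to be the more variable one

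*Protocol article*

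**What the plan says.** Data analysis (4.3.4) sets a three-way rule. It opens with "For quantitative indicators such as age" and requires a check of two conditions: "it is necessary to check whether the data meet the precondition of normality and homogeneity of variance".

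- Both hold: "If the above conditions are met, a *t* test of measurement data of group design will be adopted". I read this as the pooled two-sample t test.
- "If only normality and not homogeneity of variance are satisfied": a corrected t test, which I read as Welch or Satterthwaite.
- Neither case applies: "Otherwise, the Wilcoxon rank sum test will be used".

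The article does not say whether the check is a formal test or at what threshold. It gives no other rule for comparing quantitative data between groups. On the level, "values ≤.05 will be considered statistically significant", and "A one-sided test (validity) will be used for all major efficacy indicators".

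Determination of grouping (3.7) forms the groups "according to whether they will receive TCM treatment or not", and classifies patients only once all clinical data are in. The 1:1 ratio in Sample size calculation (3.5) is a planning assumption, not a constraint.

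**The concern.** A variance check that finds nothing at this sample size does not show that the variances are equal. Some data sets with truly unequal variances will pass and go to the pooled t test, whose standard error is then wrong unless the groups are the same size. The reported P value takes no account of the selection step. Because group sizes follow the treatment received, equal size cannot be relied on.

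At stake is the error rate of the secondary quantitative comparisons: tumor markers, symptom scores and quality-of-life scales. There is also a question of interpretation. If an outcome is compared at several visits, the rule could send one scale to a comparison of means at one visit and of ranks at the next, and those tests answer different questions.

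**Working it through.** **Inputs from the article.** The three branches and the .05 level (4.3.4); uncontrolled group sizes (3.7); totals of 134 before dropout and 148 after it (3.5). No SD is given for any outcome.

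**Assumed.** Shapiro-Wilk in each group and mean-centred Levene, both at .05; unequal splits of roughly 1:2 to 1:3.5; SD ratios from 1 to 2 in either direction.

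**The plan's own figure.** The article states no error rate for this rule beyond the nominal .05. The total that sets the scale can be checked. With 22% v 45%, two-sided .05 and 80% power, the mean rate is 0.335 and

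n per group = [1.96·√(2·0.335·0.665) + 0.84·√(0.22·0.78 + 0.45·0.55)]² / 0.23² ≈ 65.

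That is 130 in total, within 3% of the stated 134.

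**Step 1: why direction matters.** The pooled t test uses the variance s_p²(1/n₁ + 1/n₂), with s_p² = [(n₁−1)s₁² + (n₂−1)s₂²]/(n₁+n₂−2). The true variance of the difference is s₁²/n₁ + s₂²/n₂.

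- *74:74, any SDs.* The two expressions are identical.
- *37:111, smaller group's SD 1.25 times larger.* s_p² = (36·1.5625 + 110)/146 = 1.139. Variance used: 1.139·(1/37 + 1/111) = 0.0410. True: 1.5625/37 + 1/111 = 0.0512. The standard error is √(0.0410/0.0512) ≈ 0.895 of what it should be. A pooled t test used always would reject at about 2[1 − Φ(1.96·0.895)] ≈ 7.9%.
- *37:111, larger group's SD 1.5 times larger.* s_p² = (36 + 110·2.25)/146 = 1.942. Variance used: 0.0700. True: 1/37 + 2.25/111 = 0.0473. The standard error is about 1.22 times too large, and the pooled test rejects at about 1.7%.

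The plan does not always use the pooled test, since detected inequality goes to the corrected test. The error of the whole rule therefore has to be simulated.

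**Step 2: error of the whole rule.** Normal data, no true difference, two-sided 5%, 10,000 runs per setting (simulation SE about 0.2 points).

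| Split | Wider group | SD ratio 1.25 | 1.5 | 2 |
|---|---|---|---|---|
| 49:99 | smaller | 6.1% | 5.9% | 5.6% |
| 37:111 | smaller | 7.0% | 6.1% | 5.7% |
| 30:104 | smaller | 6.8% | 6.7% | not run |
| 49:99 | larger | – | 4.6% | 4.9% |
| 37:111 | larger | – | 4.5% | 4.9% |

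At 74:74 the rule gave 5.0-5.7% over all ratios. Welch without any pretest gave 4.6-5.6% in every setting.

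Splits of the 134 total, with the smaller group's SD 1.25 to 1.5 times larger (8,000 runs), agree: 6.1-6.8% at 34:100 and 5.7-6.6% at 45:89.

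One-sided at .05, the rule gave about 5.3-6.4% when the smaller group is wider and 4.3-5.2% when the larger group is wider.

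**Step 3: non-normal data.** With symmetric heavy tails (t, 5 df, ratios up to 2), the rule gave 5.4-7.6% when the smaller group is wider and 3.4-3.9% when the larger group is. With clearly skewed data (gamma, skewness 1, equal means), about 98% of runs at 37:111 went to Wilcoxon.

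**Step 4: power given up by Welch.** Equal SDs, 0.5 SD effect: 81.7% v 81.7% (67:67), 77.6% pooled v 77.3% Welch (45:89), 70.6% v 69.9% (34:100). The largest loss is 0.7 points.

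**The case against.** The case for leaving the rule alone is fair in several respects.

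- **The plan already holds most of the remedy.** Detected unequal variances go to a corrected t test. This stands, and it is why the excess is only 1-2 points.
- **Unequal spread is nowhere stated.** A reader might infer that this cohort is bound to produce the harmful pattern. Section 3.7 supports unequal size only; no section gives an SD or suggests that the smaller group will be the wider one.
- **The level is not exceeded whenever size and spread both differ.** A reader might take it that way, but when the larger group is more variable the rule stays at or below 5%.
- **Larger figures are easy to misread.** Among data sets that pass Levene at 34:100, the pooled test rejects 8.0% (SD ratio 1.25) to 10.3% (ratio 1.4). Those rates are conditional on passing and are not the error of the stated rule. Skewed data with equal means give up to 18.5% at 37:111, but that excess arises because Wilcoxon does not test equal means. It also appears with equal groups (9.6% at 74:74, ratio 1.5), so it is not an effect of pretesting.
- **Scope is partly inferred.** The rule's only example is age, a baseline variable. Since no other rule is given for quantitative data, applying it to the secondary scores is the natural reading, but it is not explicit. Visit-by-visit testing is not specified either, so switching between means and ranks is a possibility and not a stated feature.
- **The check may be informal.** The article names no test. An informal check is still data-driven, but its error cannot be calculated.

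What remains is that a test chosen from the data has no guaranteed level when group sizes are uncontrolled, and a simpler rule avoids this at almost no cost.

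**Conclusion.** The point holds as a low-severity improvement. The article fixes a data-driven choice of test while leaving group sizes uncontrolled, so the nominal 5% is not assured for secondary quantitative comparisons. If the smaller group is the more variable one and the data are normal, the two-sided error is about 6-7% and the one-sided error about 5.3-6.4%. With equal groups, or with the wider spread in the larger group, there is no material excess. These sizes rest on assumed splits, SD ratios and pretests. The inference that the main result is compromised is not supported: overall survival is compared by log-rank, outside this rule.

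**What to change.** In section 4.3.4, replace the three-way rule with two sentences to this effect:

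> Two-group comparisons of means use the unequal-variance (Welch) t test, without preliminary tests of normality or variance. Outcomes to be compared by the Wilcoxon rank sum test or after log transformation are listed here in advance, and each outcome keeps the same method at every visit.

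The second sentence matters for markedly skewed measures, which may include the tumor markers. With exponential data at 37:111, Welch's two-sided error was 4.7-6.7%, but its one-sided error reached about 8.5% in one direction. Such outcomes should be placed on the rank or log-scale list before the data are seen.

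The cost is a short text change; SPSS already prints the unequal-variance line. The downside is under 1 point of power when variances are truly equal (at most 0.7 points in the settings above).

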### Study setting and design

3.1

This study is a multicenter, prospective cohort study on the clinical efficacy of integrated traditional Chinese and Western medicine in the treatment of pancreatic cancer. It was launched in April 2019 and is scheduled to end in October 2021 with enrollment to be completed by June 31, 2020. All cases will be collected at 12 medical units including Guang’anmen Hospital, China Academy of Chinese Medical Sciences, Henan Provincial Cancer Hospital, Jining No.1 People's Hospital, Jiangsu Provincial Hospital of Chinese Medicine, Zhejiang Provincial Hospital of TCM, Yueyang Hospital of Integrated Traditional Chinese and Western Medicine, Shanghai University of Traditional Chinese Medicine, Tongde Hospital of Zhejiang Province, Wangjing Hospital of CACMS, Xiyuan Hospital CACMS, Chongqing Cancer Hospital, Gansu Provincial Cancer Hospital, and Shanxi Provincial Cancer Hospital. A total of 148 patients will be admitted to the treatment group with Western medicine and the integrated treatment group with traditional Chinese and Western medicine. The study schema and the flow chart are presented in Fig. 1. Inclusion and exclusion criteria are presented in Table 1. Two investigators will be responsible for the follow-up of each participant at baseline and every 6 weeks ± 1 week, and the data collection schedule is presented in Table 2.

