#### Overall survival (OS)

4.1.1

The primary outcome of this study is OS, which is from enrollment to patient death or the end of the study (October 31, 2021).

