### Strengths

5.1

This study has several advantages. First, this is a multicenter prospective observational cohort study involving 12 medical units in 9 provinces and cities in China, all of which are grade-3A hospitals. The results are reliable and can provide relatively objective evidence. Second, observational studies are more humane than randomized controlled trials (RCT). Moreover, it will lay a foundation for the standardization of integrated Chinese and Western medicine treatment to improve the curative effect, reduce the medical expenses of pancreatic cancer and the abuse and reuse of drugs, and generate certain social benefits for more patients with pancreatic cancer. This study involving 12 medical units in 9 provinces and cities in China, all of which are grade-3A hospitals, will generate relatively reliable results.

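### Overall survival, the primary outcome, is compared between non-randomised treatment groups by an unadjusted log-rank test, so prognostic differences can pass for a TCM effect or hide one

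*Protocol article*

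**What the plan says.** The Strengths section describes the design: "First, this is a multicenter prospective observational cohort study involving 12 medical units in 9 provinces and cities in China". Section 3.7 (Determination of grouping) divides patients "according to whether they will receive TCM treatment or not", and the classification is "based on the time of exposure after all clinical data are collected, not set at the time of enrollment". Nothing in the design balances prognosis between the two groups.

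Section 4.1.1 makes overall survival, counted from enrollment, the primary outcome. Section 4.3.4 (Data analysis) gives the method for comparing it: "The log-rank test will be used to compare the survival rate, and the corresponding survival curve will be obtained". The same section tests major efficacy indicators one-sided, with P values up to .05 counted as significant. Its t, Wilcoxon, chi-square and Fisher tests are for variables such as age and sex, and do not enter the survival comparison.

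A second paragraph of 4.3.4 brings in a Cox model: "For the analysis of influencing factors of efficacy, the univariate Cox regression model will be adopted in the first screen". Variables pass at P < .10 and then enter a multivariable model judged at P < .05. No covariate is named, and the text does not say that TCM exposure is in the model.

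The Limitations section discusses sample size, study duration and funding, but not confounding.

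**The concern.** A log-rank test between two groups answers a causal question only if the groups would have had the same survival without the treatment difference. Randomisation would justify that; grouping by treatment received does not. If the groups differ at baseline in stage, performance status or tumour burden, the crude test mixes those differences with any effect of TCM. It then neither holds its nominal error rate nor estimates the effect of adding TCM.

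The primary conclusion is at stake. Section 2 says the results are to support an integrated treatment plan, and an investigator could follow 4.3.4 to the letter and conclude efficacy from the crude log-rank P value alone.

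**Working it through.** **The plan's own figure.** The plan gives no number for confounding; its only relevant figures are those of the sample size. With 1-year survival of 22% and 45%, two-sided alpha 0.05 and power 80%, the pooled two-proportion formula gives

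n per group = [1.960·√(2·0.335·0.665) + 0.842·√(0.22·0.78 + 0.45·0.55)]² / 0.23² = 64.9, so 65 per group and 130 in total.

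That is close to the stated 134. The calculation contains no term for confounding. The check below uses the recruitment target: 148/2 = 74 per group.

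**Inputs.**
- From the article: 74 per group; accrual April 2019 to June 2020 (15 months); end of October 2021 (month 31); Western-medicine median survival of 6 to 11 months.
- Assumed: a median of about 8 months, exponential survival, a true TCM hazard ratio of 1, and one binary prognostic factor. The factor's strength and its prevalence in each group are not in the article, so a range is shown.

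**Step 1: events.** Follow-up runs from 16 to 31 months. The mean event probability is 1 − [(8/ln 2)/15]·(2^(−16/8) − 2^(−31/8)) = 1 − 0.769·(0.250 − 0.068) = 0.86. This gives about 148 × 0.86 = 127 deaths.

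**Step 2: apparent hazard ratio.** For a factor with hazard ratio h and prevalence p_I (integrated) and p_W (Western), the crude ratio at the start of follow-up is [1 + p_I(h − 1)] / [1 + p_W(h − 1)].

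**Step 3: chance of declaring TCM effective.** The log-rank statistic is shifted by ln(HR)·√(127/4) = 5.635·ln(HR). The one-sided rejection rate is Φ(−1.645 − shift).

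| h | Integrated / Western | Step 2 | Crude HR, simulated | Step 3, from simulated HR | One-sided rate, simulated |
|---|---|---|---|---|---|
| 1.5 | 45% / 55% | 1.225/1.275 = 0.96 | 0.96 | Φ(−1.415) = 8% | about 7% |
| 2.0 | 40% / 60% | 1.4/1.6 = 0.875 | 0.88 | Φ(−0.925) = 18% | 18% |
| 2.0 | 30% / 60% | 1.3/1.6 = 0.81 | 0.82 | Φ(−0.527) = 30% | 29% |
| 2.0 | 60% / 40% (reversed) | 1.6/1.4 = 1.14 | 1.14 | Φ(−2.383) = 1% | 1% |

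The simulations generated individual patients under the inputs above and agree with the hand formulas. With balanced groups the test rejects in about 5% of trials. Two-sided at .05, the 40/60 and 30/60 rows give about 11% and 19%. A Cox model containing exposure and the factor, fixed in advance, returned a hazard ratio of about 1.00 and an error rate of about 5–6%.

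**Scale.** Under proportional hazards the planned 22% and 45% imply a hazard ratio of ln 0.45 / ln 0.22 = 0.53. A spurious 0.82 is ln 0.82 / ln 0.53 ≈ 31% of the planned effect on the log scale.

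**The case against.** **The Cox model may already adjust.** TCM is the one exposure of this cohort and a natural candidate in a search for influencing factors. If it passed the screen, the multivariable model would give an adjusted hazard ratio, and a factor as strong as h = 2.0 would usually pass P < .10 with 148 patients. This stands in part: it would be wrong to say the plan contains no multivariable analysis. But the article does not say that exposure enters. Exposure or a confounder that misses P < .10 is dropped, and a confounder that masks a TCM effect can itself cause exposure to fail the screen. Nor does the text rank this model above the log-rank test.

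**The article is condensed.** Covariate lists and centre effects may sit in an analysis plan that is not shown, and their absence is not the point here. The article itself fixes an unadjusted test as the comparison for the primary outcome.

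**Direction is unknown.** A reader might infer that fitter patients choose TCM, or that the type of hospital decides who receives it, so that the result will be biased in favour of TCM. The article does not support this. It says only that grouping follows treatment received. It lists the sites ("All cases will be collected at 12 medical units") without saying which group each contributes to, and its eligibility table is not shown. The reversed row shows that the bias can equally run against TCM.

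**Conclusion.** The point holds: as written, the primary comparison cannot separate a TCM effect from baseline differences between groups, and the P-screened Cox model does not make up for that.

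The size depends on assumptions about a single binary factor. A small imbalance does little (HR 0.96, about 7%). Imbalances of 20 to 30 percentage points in a factor that doubles the hazard raise the one-sided false-positive rate to about 18–29%, or lower it to 1% when reversed. Several imbalanced factors can combine: three with hazard ratio 1.4 each, at 40% versus 60%, give about 0.82, since (1.16/1.24)³ = 0.82. None of these scenarios alone reproduces the planned effect of about 0.53, but they are enough to produce a significant result by confounding or to hide a modest real effect. The documents do not show that such an imbalance exists or which way it would run; they show that the stated test offers no protection if it does.

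**What to change.** In section 4.3.4:

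- Make the primary comparison of overall survival a Cox model with TCM exposure forced in and a short list of baseline covariates fixed in advance, not chosen by P value: stage III/IV, ECOG, CA199 and age. Handle centre by stratification, a random effect or cluster-robust variance. Propensity-score weighting on the same covariates is an acceptable alternative.
- Report the log-rank test and crude survival curves as descriptive.
- Label the P-screened Cox model as exploratory.

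The article already specifies staging, ECOG and CA199 and names age as a variable. About 127 expected deaths can carry a list of this length. No new patients are needed. The cost is some rewording and slightly more analysis; the estimate may shrink or its interval widen.

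Baseline adjustment does not solve a separate problem. The integrated group must reach "TCM treatment ≥12 weeks, times of chemotherapy ≥2 courses" while survival is counted from enrollment, which gives that group guaranteed survival time. That immortal-time problem in the grouping rule needs its own remedy.
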